**(Amended January 17, 2003)**

## Final analyses

### Analysis of demographics

Demographic characteristics (age, sex, race) of each study cohort will be tabulated.

The mean age (plus range and standard deviation) by sex of the enrolled subjects, as a whole, and per group, will be calculated.

The distribution of the subjects enrolled among the study sites will be tabulated as a whole and per group.

### Analysis of efficacy

#### Calculation of time at risk

***First surveillance period*** *(Double-blind phase up to day 256, month 8½)*

For each subject in the ATP and Total cohorts, time at risk begins 14 days after the third vaccination while the time at risk for each subject in the ITT cohort begins on day of first vaccination (day 0).

For evaluation of the primary endpoint, end of the time at risk will be the first clinical malaria episode fitting the primary case definition, or on the last day of the surveillance period (day 256, month 8½) if no episode has occurred prior to this. A similarly approach will be used for the other “time to” analyses, which include the secondary endpoint for time to infection (with respect to Cohort 2) and secondary endpoints examining different case definitions of malaria (with respect to Cohort 1). The end of time at risk is determined in the same way for all cohorts (ATP, Total and ITT).

For the evaluation of efficacy against multiple attacks the time at risk will extend to month 8½ and be applied to all cohorts (ATP, Total and ITT).

Time at risk will be adjusted for absence from the study area and anti malaria drug therapy. The monthly home visits will be used to determine any period of travel outside the study area. Absences from the study area of 2 weeks or more will be recorded in multiples of 1 week. The date of departure will be documented. Similarly if treatment for malaria is administered, the subject will not be considered susceptible to malaria infection for a duration 28 days and this period of time will be deducted from the time at risk.

If a subject is lost to follow-up, withdraws or dies, the observations for that subject will be censored at date of withdrawal or death; or at the midpoint between two monthly home visits if the date of withdrawal or death are not available.

***Subjects will be removed from the risk set when they are not at risk by censoring the records and returned to the risk set at a later time. Commercially available software can fit a Cox model, assuming that, in the analysis data set, each subject is represented by one or more observations, each consisting of a time interval, disease and other covariate values of interest over the time interval.*(Amended January 17, 2003)**

***Second surveillance period*** *(Single-blind phase up to month 21)*

During the second surveillance period the time contributed by each individual to the time at risk for each endpoint will be determined in a similar way to the methodology given for that in the first surveillance period. For the ATP and Total cohorts two periods are examined for the endpoints: from month 8½ until month 21 and from month 2½ until month 21. These are specified for each endpoint in the section 10.4. ***For the ITT cohort, the period from day 0 (first vaccination) until month 21 will be examined for the endpoints corresponding to the second surveillance period.***

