Other measures of vaccine efficacy have been included as secondary endpoints. The range of clinical case definitions for malaria encompass a range of disease severity. The endpoint of history or documented fever plus any level of parasitemia may be relatively non-specific, but represents the large number of children, who attend health centres and require anti-malarial treatment, and is therefore of interest to public health. The definition incorporating high levels of parasitemia (15 000 per µl) represents disease at the more severe end of the spectrum and is highly specific (95%), but less sensitive (87%). Malaria parasite density may be a good assessor of a partially effective vaccine, which may act by controlling the level of parasitemia.

Children’s haematocrits fall in association with clinical attacks of malaria and the haematocrit is therefore a measure that reflects the cumulative frequency and severity of malaria episodes. At the cross-sectional surveys at months 8½ and 21, children will all be assessed with a blood slide for malaria parasite density and a haematocrit. Haematocrit below 25% is moderate anaemia that warrants treatment and a value of below 15% is severe anaemia and is frequently life-threatening[[18]](#endnote-19). If the vaccine showed efficacy against moderate anaemia, it is likely that it would also show efficacy against severe malaria anaemia.

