***Efficacy***

- The time to the first clinical episode of symptomatic *P falciparum* malaria (Secondary Case Definition 1 as defined in section 10.1) detected by passive case detection over a 6 month observation period starting 14 days after dose 3 (day 90) in children (1-4 years of age at first vaccination) who have received RTS,S/AS02A malaria vaccine or one of the control vaccine schedules (either hepatitis B vaccine or *Haemophilus influenzae* type b vaccine and 7-valent pneumococcal conjugate vaccine).
- The time to the first clinical episode of symptomatic *P falciparum* malaria (Secondary Case Definition 2 as defined in section 10.1) detected by passive case detection over a 6 month observation period starting 14 days after last vaccination (dose 3) in children (1-4 years of age at first vaccination) who have received RTS,S/AS02A malaria vaccine or one of the control vaccine schedules (either hepatitis B vaccine or *Haemophilus influenzae* type b vaccine and 7-valent pneumococcal conjugate vaccine).
- The time to the first clinical episode of symptomatic *P falciparum* malaria (Secondary Case Definition 3 as defined in section 10.1) detected by passive case detection over a 6 month observation period starting 14 days after last vaccination (dose 3) in children (1-4 years of age at first vaccination) who have received RTS,S/AS02A malaria vaccine or one of the control vaccine schedules (either hepatitis B vaccine or *Haemophilus influenzae* type b vaccine and 7-valent pneumococcal conjugate vaccine).
- The total number of clinical episodes of symptomatic *P falciparum* malaria (according to the Primary Case Definition for malaria episodes as defined in section 10.1) over the time at risk (as defined in section 10.7.2.1) during the 6 -month surveillance period (month 2½ to month 8½ inclusive).
- The time to the first presentation at Manhiça District Hospital with anaemia (Anaemia Case Definition as defined in section 10.1) over a 6 month observation period starting 14 days after last vaccination (dose 3) in children (1-4 years of age at first vaccination).
- Presence of anaemia in children (1-4 years of age at first vaccination) (Anaemia Case Definition as defined in section 10.1) at 6½ months after dose 3 (month 8½).
- The number of asexual stage falciparum parasites per µl of blood for each subject at 6½months after dose 3 (month 8½).

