**(Amended January 17, 2003)**

#### Vaccine efficacy

##### Cohort 1: primary and secondary endpoints

Time to first symptomatic *P. falciparum* malaria over a 6 month period starting 14 days after dose 3 will be examined using Kaplan-Meier curves for both groups and these will be compared using the log-rank test or Wilcoxon test. Cox regression will be used to assess the significance of the group effect and the vaccine efficacy (defined as 1-R, where R is the hazard ratio [RTS,SAS02A:control vaccine]) will be estimated from the hazard ratio of the RTS,S/AS02A group versus the Control group (with 95% CI) adjusting for prognostic/stratifying factors (see section 10.7.2.2.7).

Cox regression assumes proportional hazards throughout the follow-up period. This assumption will be checked by plotting the log of the cumulative hazard against the log of time. Scaled Schonfield residuals may also be plotted to assess extent of non-proportionality of the hazard over time. If there is strong evidence that the hazard ratio is not constant over the surveillance period then alternative approaches to analyse the data will be examined:

- The 6 month surveillance period will be partitioned into three periods based on equal number of events and piecewise Cox regression models fitted to each.
- Cox regression model with time varying covariates.
- Alternative model formulations e.g. accelerated failure time models.

The other secondary endpoints for the evaluation of vaccine efficacy use distinct definitions of clinical episodes. The same procedures as described above will be used to evaluate these clinical case definitions.

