##### Exploratory analyses

*Intention-to treat analysis for vaccine efficacy*

***An intention-to-treat analysis will be conducted for all clinical efficacy endpoints incorporating a “time to” analysis (as defined in sections 10.2, 10.3 and Table 4) for the periods of time at risk as defined in section 10.7.2.1. The methodology to be used for this analysis is detailed in section 10.7.2.2.1.***

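### As worded, the 28-day post-treatment deduction in section 10.7.2.1 also reaches time to first anaemia presentation, so first anaemia presentations on days 1–28 after malaria treatment would not be counted

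*Supplement*

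**What the plan says.** Section 10.7.2.1 states the adjustment in general terms: "Time at risk will be adjusted for absence from the study area and anti malaria drug therapy". For a child given malaria treatment it says: "not be considered susceptible to malaria infection for a duration 28 days and this period of time will be deducted from the time at risk". The mechanism is explicit: "Subjects will be removed from the risk set when they are not at risk by censoring the records", with return to the risk set later. An event inside the window therefore has no record to attach to.

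The anaemia endpoint is in section 10.3.1: "The time to the first presentation at Manhiça District Hospital with anaemia", over the six-month observation period. Its case definition, haematocrit below 25%, is a row of Table 4.

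Section 10.7.2.1 does not name anaemia. It says a similar approach applies to the other time-to analyses, and its examples are time to infection in Cohort 2 and the alternative malaria case definitions in Cohort 1. The examples are introduced as included items, so the list is open. Two other places bear on scope:

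- Section 10.7.2.2.1 carries the primary-endpoint procedures over to the remaining secondary efficacy endpoints: "The other secondary endpoints for the evaluation of vaccine efficacy use distinct definitions of clinical episodes".
- Section 10.7.2.2.9, on the intention-to-treat analysis, covers all clinical efficacy endpoints analysed as time to event, and describes this as "analysis (as defined in sections 10.2, 10.3 and Table 4) for the periods of time at risk as defined in section 10.7.2.1". Both 10.3 and Table 4 contain anaemia.

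On the link between malaria and anaemia, section 1.2.2.1.1 states: "haematocrits fall in association with clinical attacks of malaria and the haematocrit is therefore a measure that reflects the cumulative frequency and severity", meaning that of the child's attacks.

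**The concern.** The reason for the window does not carry over. A child protected from new parasitaemia for 28 days after treatment can still present with a low haematocrit, and on the protocol's own account a low haematocrit is what a recent attack tends to produce. A child treated on day 100 who first presents with haematocrit 20% on day 112 would contribute no event.

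Entry to the window is broad. Section 5.2.6 treats every child with fever or a history of fever and any parasitaemia, which is wider than the primary case definition.

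Clinically presenting anaemia is part of a stated secondary efficacy objective (section 2.2.1), on an endpoint that the protocol itself powers below 80%. If the vaccine reduces treated attacks, more control than vaccinated children pass through the window, and more control events go uncounted.

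**Working it through.** **Inputs from the protocol (sections 10.6.1 and 10.7.2.1).** 704 evaluable children per group; control attack rate 11%; vaccine efficacy (VE) 50%; anaemia 6% in controls against 3% in the vaccine group over six months; two-sided log-rank test at 0.05; stated power 68%; 28-day window; surveillance from day 74 to day 256, which is 182 days.

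**Inputs not in the documents (assumed).** f is the share of control anaemia linked to a treated attack, taken as 25%, 50% or 90%. w is the share of those linked cases that first present on days 1–28 after treatment, taken as 25%, 50% or 75%, with the rest found at the attack visit.

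**1. The plan's own power figure.** Expected events are 704 × (0.06 + 0.03) = 63.4. The hazard ratio is ln(0.97)/ln(0.94) = 0.492. Schoenfeld power is Φ(½√63.4 × |ln 0.492| − 1.96) = Φ(0.86), about 80.5%. Freedman's log-rank formula gives 77.3% and a two-proportion test 77.6%. The stated 68% does not follow from its inputs; it errs on the cautious side and is a separate matter. Power loss in step 4 is measured from 77.6%.

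**2. How many children enter a window.** From first primary-definition attacks alone: controls 0.11 × 704 ≈ 77, vaccine group 0.055 × 704 ≈ 39, about 2 to 1. The wider treatment trigger makes the true numbers larger. The control windows take 77 × 28 = 2,156 of 704 × 182 = 128,128 child-days, or 1.7%, so the person-time removed is small.

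**3. Effect on the estimate.** Suppose the vaccine halves attack-linked anaemia and leaves other anaemia unchanged. Per unit of control anaemia, ignoring the small person-time correction:

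- All cases counted: VE = 1 − [(1 − f) + f/2] = f/2.
- Under the rule, controls keep 1 − fw and the vaccine group keeps (1 − f) + f(1 − w)/2, so VE = f(1 − w) / [2(1 − fw)].

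| f | VE, all counted | VE under rule, w = 25% | w = 50% | w = 75% |
|---|---|---|---|---|
| 25% | 12.5% | 10.0% | 7.1% | 3.8% |
| 50% | 25.0% | 21.4% | 16.7% | 10.0% |
| 90% | 45.0% | 43.5% | 40.9% | 34.6% |

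For example, f = 50% and w = 75% gives 0.5 × 0.25 / (2 × 0.625) = 10.0%. A simulation with event times and person-time agrees to within about 1.5 points: roughly 12% becomes 4–11%, 24% becomes 9–21%, and 45% becomes 35–44%. The attenuation runs from about 1 to about 15 points. In the simulation about 3 to 26 control events are lost, against about 1.4 to 13 in the vaccine group.

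**4. Effect on power.** If both arms lose the same proportion of events, the hazard ratio is unchanged and only power falls. By the two-proportion test at 6% against 3%, losses of 10%, 20%, 30% and 40% reduce 77.6% to 73%, 68%, 62% and 55%.

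**5. Plausibility of the upper cells.** With 0.06 × 704 = 42.2 control cases, f = 50% and w = 75% puts 42.2 × 0.375 ≈ 16 in the window. That would be about one in five of the 77 treated controls newly presenting with anaemia within 28 days. The upper end of the range therefore needs strong assumptions, or many more treated children than 77.

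**The case against.** The strongest reply is that the reach of the rule is inferred. Section 10.7.2.1 lists infection and malaria case definitions and does not name anaemia. The 28-day sentence gives a reason about infection that could be read as limiting it to infection and malaria endpoints. Section 10.7.2.2.1 speaks of clinical episodes, and the one explicit tie is in the exploratory intention-to-treat analysis. The RAP, not among the documents, could settle the matter before unblinding. All of this is fair, and it means anaemia is covered by general wording rather than by name. But the list is open, no exemption is written, and a RAP that followed the protocol would apply the deduction. If 10.7.2.1 did not govern anaemia, the endpoint would have no time-at-risk rule at all. Either reading needs the clarifying sentence.

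The second reply is that much malaria-linked anaemia is still counted. Section 5.2.6 takes a haematocrit at every attendance with fever or a history of fever, so anaemia found at the attack visit precedes the window. Children re-enter after 28 days, and the month 8½ prevalence endpoint uses no time at risk. This stands in full. A reader might infer that the rule removes malaria-caused anaemia generally; only first presentations on days 1–28 are lost.

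The third reply is that unequal event loss is not in itself bias, because events and person-time leave together. This also stands. If efficacy is the same inside and outside the window, twice as many control events are lost, yet the hazard ratio is unaffected. Bias toward zero requires the lost events to be more vaccine-preventable than those kept.

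**Conclusion.** The point holds as a gap in wording with a modest analytic consequence. As written, the deduction extends to an endpoint its stated reason does not fit, and first anaemia presentations on days 1–28 after treatment would go uncounted. Fewer events is the sure effect if any child first presents in that window. The larger loss among controls depends on the vaccine reducing treated attacks; with no efficacy the loss is balanced. Attenuation depends further on the lost events being more malaria-linked than those kept.

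Neither the share of anaemia linked to treated attacks nor its timing is in the documents, so the 1 to 15 points is a range over assumptions and not an estimate. A reader might infer that anaemia efficacy would be estimated as zero. In the formula above that needs w = 100%, meaning no attack-linked anaemia at the attack visit, and also none after day 28; section 5.2.6 gives no support for that. At the other extreme, f = 100% with w below 100% leaves the estimate at 50% and costs only power.

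The primary endpoint, on which the development decision rests, is not affected, and the error would understate efficacy rather than inflate it.

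**What to change.** State in section 10.7.2.1, and repeat in the RAP, that the 28-day post-treatment deduction applies only to the malaria-episode and infection endpoints. For time to first clinical presentation with anaemia, keep treated children in the risk set and adjust only for absence from the study area, withdrawal and death. The version with the 28 days deducted can be kept as an optional sensitivity analysis.

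The cost is one sentence in each document. It needs no new data or visits and changes neither treatment nor the primary analysis. Time at risk for this one endpoint becomes slightly longer, by about 1.7% of control child-days at the design attack rate.

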**(Amended January 17, 2003)**

#### Vaccine efficacy

##### Cohort 1: primary and secondary endpoints

Time to first symptomatic *P. falciparum* malaria over a 6 month period starting 14 days after dose 3 will be examined using Kaplan-Meier curves for both groups and these will be compared using the log-rank test or Wilcoxon test. Cox regression will be used to assess the significance of the group effect and the vaccine efficacy (defined as 1-R, where R is the hazard ratio [RTS,SAS02A:control vaccine]) will be estimated from the hazard ratio of the RTS,S/AS02A group versus the Control group (with 95% CI) adjusting for prognostic/stratifying factors (see section 10.7.2.2.7).

Cox regression assumes proportional hazards throughout the follow-up period. This assumption will be checked by plotting the log of the cumulative hazard against the log of time. Scaled Schonfield residuals may also be plotted to assess extent of non-proportionality of the hazard over time. If there is strong evidence that the hazard ratio is not constant over the surveillance period then alternative approaches to analyse the data will be examined:

- The 6 month surveillance period will be partitioned into three periods based on equal number of events and piecewise Cox regression models fitted to each.
- Cox regression model with time varying covariates.
- Alternative model formulations e.g. accelerated failure time models.

The other secondary endpoints for the evaluation of vaccine efficacy use distinct definitions of clinical episodes. The same procedures as described above will be used to evaluate these clinical case definitions.

##### Cohort 1: secondary endpoint for estimation of vaccine efficacy given multiple episodes per subject

One of the secondary endpoints is the total number of clinical episodes of symptomatic *P. falciparum* malaria over the time at risk during the 6 month surveillance period (months 2½ to 8½ inclusive) (see section 10.3.1).

The analysis of multiple episodes can be handled within the Cox Model framework available in many commercially-available software packages. The ordinary Cox regression estimate of variance for the coefficients treats each observation as independent. This assumption does not hold when a subject can present multiple episodes. An adjustment to the variance estimate to account for the inter-subject correlation has to be made. This can be achieved by using the jackknife to derive a robust variance estimate for the Cox model[[36]](#endnote-37). This is equivalent to the Lin and Wei sandwich estimator for the Cox model[[37]](#endnote-38). The basic procedure is to fit the ordinary Cox model - initially ignoring the correlation - followed by correcting the naïve variance estimate. This approach can fit within commercially available software.

##### Cohort 1: tertiary endpoints for cumulative incidence

The cumulative incidence (subjects with at least one episode of symptomatic *P. falciparum* malaria during the surveillance) over the periods from month 8½ to month 21 and from months 2½ to month 21 will be compared between both groups using Kaplan-Meier curves and Fisher’s Exact test (two-sided) at month 21.

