##### Clinical disease

The primary case definition for the trial was chosen with the following considerations in mind. It was important that it represents true cases of malaria at the more severe end of the disease spectrum. Therefore, cases contributing to the primary case definition are children who have been judged to be ill by their parents and brought for treatment to their local hospital or health facility. These cases are defined as febrile ( 37.5°C) with a parasitaemia level above a cut off value. In malaria endemic areas parasitaemia is common in the absence of symptoms. This means that sick children with a range of conditions may have coincidental parasitaemia, but that this is not the cause of the illness. Methodology proposed by T. Smith models the relationship between parasite density and fever in a population and defines a threshold above which the parasitaemia is likely to be the cause of the fever. In this population this was determined as 2500 parasites per µl and using this definition, the case definition has been estimated to be 91% specific and 95% sensitive[[17]](#endnote-18). The high specificity will ensure that the estimate of effect is not a significant underestimate of the true vaccine efficacy.

The primary endpoint is time to first clinical attack, which is a suitable method for assessing the efficacy of a vaccine inducing partial immunity to malaria. This type of vaccine, which gives partial protection to most vaccinees (rather than a vaccine that protects completely a proportion of the population) cannot be assessed using a comparison of the proportions of people affected because over time, as progressively more subjects experience their first attack, the measured efficacy will trend to zero.

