***Efficacy***

- The total number of clinical episodes of symptomatic *P falciparum* malaria (according to the Primary Case Definition for malaria as defined in section 10.1) over the time at risk (as defined in section 10.7.2.1) during the open surveillance period (months 8½ to 21).
- The total number of clinical episodes of symptomatic *P falciparum* malaria (according to the Primary Case Definition for malaria as defined in section 10.1) over the time at risk (as defined in section 10.7.2.1) during the complete surveillance period (months 2½ to 21).
- Presence or absence of anaemia in children aged 1-4 years of age at first vaccination (Anaemia Case Definition as defined in section 10.1) at month 21 (day 630).
- The number of asexual stage falciparum parasites per µl of blood for each subject at 19 months after dose 3 (month 21).

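### Two Cohort 1 tertiary endpoints count all malaria episodes over time at risk, but the analysis section for them compares only the proportion of children with at least one episode

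*Supplement*

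**What the plan says.** Section 10.4.1 (and the Synopsis) lists four tertiary efficacy endpoints for Cohort 1. Two are the total number of clinical episodes meeting the primary case definition: one "over the time at risk (as defined in section 10.7.2.1) during the open surveillance period (months 8½ to 21", the other "over the time at risk (as defined in section 10.7.2.1) during the complete surveillance period (months 2½ to 21". Section 10.7.2.1 sets out time at risk for both periods. It deducts recorded absences from the study area and 28 days after malaria treatment, and gives censoring rules for loss, withdrawal and death.

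The analysis section for these endpoints is 10.7.2.2.3. Its quantity is cumulative incidence, explained as "subjects with at least one episode of symptomatic" malaria, which "will be compared between both groups using Kaplan-Meier curves and Fisher’s Exact test (two-sided) at month 21". It names no episode count, person-time denominator, rate or hazard ratio, efficacy estimate or confidence interval.

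Section 10.7.2.2.2 does have a method for repeated episodes: "The analysis of multiple episodes can be handled within the Cox Model framework available in many commercially-available software packages", with a jackknife (Lin–Wei) robust variance. It is written for the 6-month secondary endpoint only.

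Section 1.2.2.1.1, explaining the choice of a time-to-first-episode primary endpoint, says that a vaccine giving partial protection to most recipients "cannot be assessed using a comparison of the proportions of people affected because over time, as progressively more subjects experience their first attack". The consequence it draws for such a comparison is that "the measured efficacy will trend to zero".

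**The concern.** The endpoint is an episode rate and the analysis is a risk comparison. Fisher's test has no place for a second or third episode, and no place for the absence, post-treatment and censoring rules that section 10.7.2.1 sets up for these periods. It also needs every child classed as case or non-case at month 21, and section 10.7.2.2.3 does not say what happens to a child lost earlier. Because no efficacy estimate is specified, the tertiary objective of assessing efficacy against clinical episodes would have a p-value and two curves, but no effect size for the endpoint as defined.

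The comparison is also of the kind that the protocol argues against, applied to its longest windows. Persistence of protection is a live question here: section 1.1.1 reports efficacy against infection in adult men falling from 71% in the first 9 weeks to 0% in the last 6.

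**Working it through.** **1. Could another section supply the missing analysis?**

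- Section 10.7.2.2.2 is limited to months 2½–8½, and section 10.7.2.1 runs time at risk for multiple attacks in the first period to month 8½.
- The exploratory intention-to-treat analysis (section 10.7.2.2.9, with the day 0 to month 21 period in 10.7.2.1) can give a Cox estimate to month 21. It covers only clinical endpoints built on a time-to analysis, citing 10.2, 10.3 and Table 4. It uses first episodes and starts at day 0, so it does not reach the total-episode endpoints of 10.4.1.
- Parasite density and anaemia at month 21, the other two tertiary efficacy endpoints, have their own analyses (10.7.2.2.4 and 10.7.2.2.5).

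Nothing resolves the mismatch.

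**2. The plan's own figure.** The protocol states no power for the tertiary endpoints. The planning inputs borrowed below are those of section 10.6.1: 11% control attack rate, 50% efficacy, 704 evaluable per group. On the log relative-risk scale, n = [(1−p₁)/p₁ + (1−p₂)/p₂] × [(z₀.₉₇₅ + z₀.₈₀)/ln(0.85/0.50)]². With p₁ = 0.11 and p₂ = 0.055 this is 25.27 × (2.802/0.5306)² = 704.5, which matches the stated 704.

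**3. What proportions would show.** Assume the 6-month attack rate A continues at constant hazard and the true hazard ratio is 0.5. Monthly hazard h = −ln(1−A)/6; at 11%, h = 0.01942. Control risk over T months is 1 − exp(−hT), vaccine risk is 1 − exp(−hT/2), and efficacy on proportions is 1 minus their ratio. With Poisson episodes, the share of control-group episodes that are repeats is 1 − risk/(hT).

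| A per 6 months | T (months) | Control risk | Vaccine risk | Efficacy on proportions | Control repeats |
|---|---|---|---|---|---|
| 11% (planned) | 12.5 | 21.6% | 11.4% | 47.0% | 11% |
| 11% (planned) | 18.5 | 30.2% | 16.4% | 45.5% | 16% |
| 7% (lowest year, 10.6.1) | 12.5 | 14.0% | 7.3% | 48.1% | 7% |
| 7% (lowest year, 10.6.1) | 18.5 | 20.0% | 10.6% | 47.2% | 10% |

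For the 18.5-month row at 11%: hT = 0.359, and 1 − 0.302/0.359 = 16%. Over both arms together the repeats are about 13%. The same formula at 6 months gives 48.5%, so the drift from 6 to 18.5 months is about 3 points.

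**4. Sensitivity to clustering.** The documents give no figure for between-child variation in risk. In a simulation with 704 per arm, 1,500 runs, 11% first-episode risk at 6 months and an assumed gamma frailty variance of 1 to 2, efficacy on proportions was 44–42% over 12.5 months and 42–39% over 18.5 months. The episode-rate analysis stayed near 50%, and 18–32% of episodes went unused.

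**5. Power.** At a true 50% reduction both approaches have at least 98% power. At an assumed 30% over 18.5 months, Fisher's test has 92% against 96% for an episode-rate comparison without frailty, and 66% against 84% with frailty variance 2.

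**The case against.** A reader might infer that the plan will report an efficacy that drifts to zero, or that it would show false waning. The documents do not support that. Section 10.7.2.2.3 plans curves and a test, not an efficacy computed from proportions; the 47% and 45.5% arise only if someone does that calculation. Even then the loss at the planned attack rate is 3 to 4.5 points, and the larger losses rest on a frailty variance that the documents do not give.

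It would also be too strong to say that Fisher's test is the only analysis, or that all the tertiary efficacy endpoints are affected. Kaplan–Meier curves are named first and can use the censoring rules, although they show first episodes only. Two of the four endpoints are unaffected. Nor does the protocol say that children lost before month 21 will be counted as non-cases; it is silent.

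Finally, a reporting and analysis plan is to be approved before unblinding and is not among the documents. It could reconcile the two sections. But this is not a detail left open for that plan: the protocol already names a method, and the method does not fit its endpoint.

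What stands is the mismatch, the unused repeat episodes and person-time in the only test, and the absence of an efficacy estimate with interval for the stated endpoints.

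**Conclusion.** The point holds as a contradiction between endpoint and analysis for two of the four Cohort 1 tertiary efficacy endpoints. As written, total episodes over time at risk would go unanalysed for months 8½–21 and 2½–21.

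The attenuation from using proportions is modest: 50% would read as about 47% over 12.5 months and 45.5% over 18.5 months. This assumes a constant hazard at 11% per 6 months and a constant hazard ratio; the 16% of control-group episodes lost as repeats also assumes Poisson episodes. The wrong estimand and the missing effect estimate are therefore better grounds for change than the size of the bias.

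Severity is moderate. The endpoints are tertiary and have no stated power, and the primary Cox analysis, on which the development decision rests, is unaffected.

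**What to change.** In section 10.7.2.2.3, or in the reporting and analysis plan before unblinding, apply the multiple-episode Cox model with robust variance from 10.7.2.2.2 to months 8½–21 and 2½–21, using the time at risk of 10.7.2.1. Report 1 − HR with 95% CI for each period. Keep the Kaplan–Meier curves as a display of first episodes. Retain Fisher's test at most as supportive, stating how children lost before month 21 are classified.

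Redefining the two endpoints in 10.4.1 as cumulative incidence would also remove the contradiction, but it would give up the repeat episodes and keep the comparison that section 1.2.2.1.1 argues against.

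The cost is a few lines of wording. The model and code are already planned for the 6-month secondary endpoint, and the time-at-risk rules for both longer periods are already written.
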